### SAIA-MOUD impact assessment

Through SAIA-MOUD’s mentored process of solution identification and testing, we hypothesize that its use will lead to rapid and sustainable improvements in MOUD service delivery and care continuity for individuals exiting jail and linking to MOUD care upon release.

#### Study population

All adults (≥ 18 years) accessing MOUD care services during the study period including those newly initiating or continuing MOUD treatment while incarcerated in King County jails and exiting to the community.

#### Exposure definition

Facilities will be considered unexposed prior to SAIA-MOUD intervention starting in their health facility and exposed thereafter. Individuals’ exposure to the intervention will be based on the exposure status of the facility in the calendar month in which they enter care (including those newly identified as eligible for MOUD and those already diagnosed with substance use disorder and on a medication for opioid use disorder).

#### Outcomes

In the main outcome – linkage to MOUD services within 30 days of release from jail (primary goal) – we will assess whether the proportion of clients who link to care (ie. receive MOUD at a referral clinic) within 30 days of release increases from the 24-month baseline period (January 2022 through December 2023) to the 24 months post-introduction of the intervention (Table 2). Linkage is defined as MOUD prescription filled or administered at the referral site. Rather than 14 days, 30 days was chosen as the review period of interest in order to capture individuals taking the recently introduced extended release injectable MOUD which are administered monthly. Since implementation preparation activities took place throughout 2024, this baseline period is excluded.

The secondary outcome analysis will assess retention in care within 30 days after initial linkage for patients in the three SAIA-MOUD clinics compared with retention in care within 30 days for all other patients linked to MOUD services in King County. Again, retention is defined as MOUD prescription filled or administered. This patient-level analysis will assess changes in the whether patients returned within 30 days after initial linkage (a binary yes/no variable) and only patients seen by providers seeing at least 10 patients in a year will be included.

Additional exploratory analyses will assess sustainment of our primary and secondary outcomes in the 12 months after our 24-month intensive implementation phase, as well as effect modification by salient client-level factors.

#### Data sources

Multiple routine data sources will be used to measure our effectiveness outcomes, which are routinely integrated into the Integrated Data Hub (IDH) which is housed jointly by Public Health—Seattle & King County (PHSKC) and King County’s Department of Community and Health Services. The IDH includes data from multiple sources of interest – including the Medicaid payer system (for which over 93% of those leaving JHS are eligible), jail booking data, and Homelessness Management Information System. With approval from the WA State Department of Health, both the Prescription Monitoring Program (PMP), and mortality data will be linked to the IDH data using a PHSKC machine learning approach, developed for another study. Data from the IDH will be cross-checked with clinic data reports generated through the EPIC system on a quarterly basis to assess data availability and completeness. Inconsistencies will be explored at the site level.

#### Power and sample size

Power estimates are for our primary analysis – to detect an impact of SAIA-MOUD on linkage to MOUD referral services within 30 days of release from JHS. Our primary analysis will be a difference in proportions test. Assuming a baseline proportion linked of 22%, and a conservative estimate of 100 people beginning or continuing MOUD in jail and releasing to the community each month (or 2,400 total releases in each of the baseline and intervention periods), we have 80% power to detect a change in the proportion linked of 3.3% percentage points or greater, and 90% power to detect a change in the proportion linked of 3.9% percentage points or greater. Power calculations were performed using the power.prop.test function in R.

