There is a critical gap in knowledge surrounding implementation strategies to improve adoption, equity, and sustainment of MOUD care cascade services in jails and linked referral clinics in the community. There is an unprecedented influx of resources in WA and nationally being directed toward implementing MOUD, referring patients on MOUD to other services during care coordination visits, and ensuring that patients are connected to MOUD upon release [21]. However, there are limited resources and attention targeting development of evidence-based implementation strategies to optimize the MOUD care cascade between carceral settings and referral clinics upon release. Carceral settings are harmful to health and often not structurally aligned with the provision of respectful healthcare [22, 23]. Thus, implementing therapeutic interventions such as MOUD in jails requires tailored strategies to address challenges that are unique to these settings. To most effectively reduce opioid overdose risk—among other harms related to criminal legal system involvement [23]—the use of incarceration should be reduced or eliminated. It is therefore critical to focus improvements on linkages to post-release services to align with public health strategies to divest from OUD criminalization. Implementation strategies that address systemic weaknesses in MOUD services between carceral settings and referral clinics are therefore urgently needed.

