## Goals and objectives

The overall goal of this study is to strengthen the quality and continuity of MOUD care across jail and community settings in King County, WA by applying and evaluating a multi-component implementation strategy – the SAIA. Our population of interest are individuals who take MOUD during incarceration in King County, WA jails (JHS) and are subsequently referred to MOUD clinics in the community upon release. We hypothesize that organizations exposed to the SAIA will actively identify modifiable barriers to completing steps in the MOUD cascade and apply locally defined innovations that will lead to measurable improvements in the care and continuity of MOUD services for their patients over and above those observed in patients referred to MOUD clinics not exposed to the SAIA intervention. Over the five-year project, we will conduct a quasi-experimental evaluation of the effectiveness of SAIA on improving MOUD care cascade quality and continuity for patients receiving care in jail and exiting to referral clinics (Aim 1); examine determinants of SAIA-MOUD adoption, implementation, and sustainment (Aim 2); and determine SAIA-MOUD’s cost and cost-effectiveness (Aim 3).

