#### Data analysis

For our primary linkage outcome we will measure the change in proportion of clients linked in two ways: 1) a difference in proportions test comparing the average share of clients linked in the baseline period to the average share of clients linked in the intervention period and 2) a non-parametric interrupted time series (ITS) analysis. For the ITS, the proportion of clients linked will be aggregated quarterly, and the model will be adjusted for covariates including sex, age, race, ethnicity and housing status at jail release, treatment experience prior to incarceration in jail and form of MOUD provided in jail.

For our secondary analysis on retention in care, patients initially linking to SAIA clinics will be matched to patients initially linking to non-SAIA clinics using propensity score matching. Variables used in the propensity score will include sex, age, race, ethnicity and housing status at jail release, treatment experience prior to incarceration in jail and form of MOUD provided in jail, in addition to the baseline period retention rate of the index provider seen following release. Our primary approach will rely on inverse probability weighting with the estimated propensity scores. We will also assess the robustness of our results using a kernel-density-based matching estimator using the propensity scores. Our estimate of interest is the average treatment effect on the treated (ATT).

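### The powered primary test credits the whole change in linkage between 2022–2023 and 2025–2026 to SAIA; the trend-adjusted analysis is neither designated primary nor powered

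*Protocol article*

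**What the plan says.** All references are to the protocol article.

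- **Power and sample size.** The power estimates are presented as being for detecting an impact of SAIA-MOUD on linkage within 30 days. The section states "Our primary analysis will be a difference in proportions test". Its inputs are "Assuming a baseline proportion linked of 22"% and "2,400 total releases in each of the baseline and intervention periods". It reports "80% power to detect a change in the proportion linked of 3.3% percentage points or greater"; the corresponding figure at 90% power is 3.9 points. No other linkage analysis is powered.
- **Outcomes and Trial status.** The baseline is January 2022 to December 2023. Calendar 2024 is excluded because preparation took place then. The start is planned for January 2025.
- **Data analysis.** Linkage change is measured in two ways. The first contrasts pooled shares: "a difference in proportions test comparing the average share of clients linked in the baseline period to the average share of clients linked in the" (the sentence goes on to name the post-introduction period). The second is a non-parametric ITS on quarterly proportions, adjusted for patient characteristics, prior treatment experience and form of MOUD given in jail.
- **Goals and objectives.** The hypothesis is an improvement "over and above those observed in patients referred to MOUD clinics not exposed to the SAIA intervention".
- **Outcomes and Data analysis, secondary outcome.** Patients of SAIA clinics are compared with patients of other clinics, using propensity scores, for retention only.
- **Background.** "There is an unprecedented influx of resources in WA and nationally being directed toward implementing MOUD", including money aimed at connecting patients to MOUD on release. The Outcomes section adds that extended-release injectables are a recent introduction.

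**The concern.** The section that defines the primary analysis says it detects an impact of SAIA. The test it names detects any difference between two calendar periods. The article itself describes outside forces acting on the same outcome over those years: new resources directed at post-release connection and a new drug formulation. A significant result could therefore come wholly or partly from these and still be reported as SAIA effectiveness. The reverse is also possible. The Background reports that opioid-related deaths in King County doubled between 2020 and 2023, so a worsening environment could hide a real benefit.

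The stakes go beyond Aim 1. The cost-effectiveness section takes its comparative effect from the linkage outcome, so a biased before-after difference, if used there, would carry into the cost-effectiveness ratios.

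**Working it through.** **Inputs.** Baseline proportion p = 0.22 and n = 2,400 per period (Power and sample size). Periods come from Outcomes and Trial status. The significance level is not stated; two-sided 5% is assumed. Annual drift g is not given; 0.25 to 2.0 points a year is assumed.

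**1. The plan's own figures.** With the variance fixed at the baseline proportion, SE = √(2 × 0.22 × 0.78 / 2,400) = 1.196 points.
- 80% power: (1.960 + 0.842) × 1.196 = 3.35 points.
- 90% power: (1.960 + 1.282) × 1.196 = 3.88 points.

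The pooled formula, with the variance changing with the second proportion, gives 3.44 and 3.99. The stated 3.3 and 3.9 are close to these. The small difference does not affect this point.

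**2. Distance between periods.** The baseline midpoint is about 1 January 2023. The intervention midpoint (January 2025 to December 2026) is about 1 January 2026. The gap is 3 years, so a drift of g points a year produces an expected difference d = 3g with no SAIA effect.

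**3. Chance that drift alone gives p<0.05.** With p̄ = p + d/2, SE₀ = √(2p̄(1−p̄)/n) and SE₁ = √([p(1−p) + (p+d)(1−p−d)]/n), the chance of declaring an increase is Φ((d − 1.96·SE₀)/SE₁).

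Example, g = 1.0: d = 0.03, p̄ = 0.235, SE₀ = 0.01224, SE₁ = 0.01223. Then (0.0300 − 0.0240)/0.01223 = 0.49 and Φ = 0.69.

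| Drift (points/year) | d (points) | P(p<0.05), no SAIA effect |
|---|---|---|
| 0.25 | 0.75 | 10% |
| 0.5 | 1.5 | 24% |
| 0.75 | 2.25 | 46% |
| 1.0 | 3.0 | 69% |
| 1.1 | 3.3 | 77% |
| 1.3 | 3.9 | 89% |
| 1.5 | 4.5 | 95% |
| 2.0 | 6.0 | 99.8% |

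These are two-sided; only at 0.25 does the lower tail add visibly (9.1% to 9.6%). Simulation with monthly binomial counts agrees within 1 point. An observed difference of about 2.4 points is already significant, which is a drift of 2.4/3 = 0.8 points a year.

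**4. What a trend-adjusted analysis can detect.** The article does not specify its non-parametric ITS in detail, so a parametric segmented model stands in: 8 baseline and 8 intervention quarters, 300 releases each, 2024 omitted, binomial variance only, common slope plus level shift.
- Quarterly variance: 0.22 × 0.78 / 300 = 0.000572.
- Quarter index t has group means 4 and 16. S_tt = 84 + 16 × 6² = 660. For the period indicator, S_pp = 4 and S_tp = 48.
- Information left for the level shift after removing trend: 4 − 48²/660 = 0.509, against 4 without a trend term.
- SE = √(0.000572/0.509) = 3.35 points, which is √(4/0.509) = 2.8 times the SE in step 1.
- Detectable shift at 80% power: 2.802 × 3.35 = 9.4 points.
- Power at 3.3 points: Φ(3.3/3.35 − 1.96) = Φ(−0.98) = 16%.

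Allowing a slope change as well gives SE 3.51, a detectable shift of 9.8 points and power of 15% at 3.3 points. In simulation, the common-slope model keeps its false-positive rate near 5% under linear drift of 0, 1.1 and 2.0 points a year.

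**The case against.** The strongest reply is that the plan does deal with trend. The ITS is listed for the same primary outcome, and it adjusts for form of MOUD, which bears directly on the extended-release injectables. That stands: no trend analysis is missing. What remains is that the power section names the other test as primary and powers only that one. Given step 4, a significant proportions test beside an inconclusive ITS is a foreseeable result, and nothing says which governs. A rule for disagreement could be left to an analysis plan, but the designation of the primary test is stated here.

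Several stronger readings are tempting but not supported:

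- *Any upward drift would be declared a SAIA effect.* At 0.25 to 0.5 points a year this happens 10% to 24% of the time; near-certainty needs about 1.5. The Background describes resources, not a measured linkage trend.
- *The stated hypothesis is never tested.* The comparison with unexposed clinics is made for retention. It is not made for linkage.
- *Quarter-to-quarter swings inflate the type I error by a known amount.* That needs a between-quarter SD, and the article gives none.

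It is also fair to object that relying on the ITS costs a great deal of power, and that a single series cannot rule out another change coinciding with January 2025. Both are true. They are reasons to state the limitation openly. They do not make the before-after test evidence of a SAIA effect.

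**Conclusion.** The point holds. The designated and powered primary test attributes the whole change in linkage between periods to SAIA and cannot separate it from background drift. A drift of about 1 point a year, with no SAIA effect, would be called significant about 69% of the time, and 1.1 points a year reproduces the change the trial is powered to detect. These figures assume linear drift, independent releases, a two-sided 5% test and the article's own 22% and 2,400. Whether drift of that size occurs is unknown from the document.

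The comparative hypothesis in Goals and objectives is addressed only on the secondary outcome. The ITS is the suitable analysis already in the plan. On the stand-in model it detects about 9 to 10 points at 80% power and has about 15% to 17% power at 3.3 points; extra variation between quarters would make that worse.

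**What to change.** Settle these before intervention-period linkage is analysed.

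1. In Power and sample size and in Data analysis, state that the claim of a SAIA effect on linkage rests on the trend-adjusted ITS. Report the proportions test as an unadjusted description of change between periods.
2. State that 3.3 and 3.9 points are detectable changes between periods, not detectable SAIA effects. Give the detectable effect of the ITS as it will actually be fitted.
3. In Goals and objectives, limit the comparison with unexposed clinics to retention.

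Two apparent remedies should not be used. A linkage contrast between SAIA and other clinics fails because SAIA also runs in the jail, so all patients are exposed before release, and the linkage denominator in Table 2 is all releases on MOUD. Counting 2024 as unexposed, to gain precision, conflicts with the Outcomes section, which excludes that year for preparation activities.

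**Cost.** The changes are to wording; data and planned analyses stay the same. The price is a much less favourable stated detectable effect, and an acknowledged inability to exclude other changes around January 2025.

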**Table 1 Tab1:**
[figure not shown]
SAIA-MOUD study timeline

Key: SAIA-MOUD: Systems Analysis and Improvement Approach for the Medications for Opioid Use Disorder Care Cascade, *UW* University of Washington, *IRB* Institutional Review Board, *WA* Washington, *SOPs* Standard Operating Procedures, *MCAT* MOUD Cascade Analysis Tool

**Table 2 Tab2:** SAIA-MOUD study outcomes

	**Outcome**	**Indicator**	**Numerator**	**Denominator**
Primary	Linkage	MOUD receipt ≤ 30 days of jail release	# of patients on MOUD in jail who upon release receive MOUD at a referral clinic ≤ 30 days	# of patients on MOUD in jail and released to the community
Secondary	Retention	MOUD receipt ≤ 30 days of initial linkage	# of patients on MOUD in jail who link to MOUD services upon release and subsequently return for a second receipt of MOUD ≤ 30 days	# of patients on MOUD in jail who upon release receive MOUD at a referral clinic ≤ 30 days

Covariates: sex, race, ethnicity, housing stability

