### Study setting

Our study will be conducted in King County, the most populous county in Washington State (WA), which reports rising rates of opioid-related overdose and high prevalence of OUD in carceral settings [21]. The SAIA-MOUD intervention will be introduced in four sites — 1) King County Jail Health Services (JHS) which is co-located across two jail-based clinics (King County Correctional Facility’s (KCCF) and Maleng Regional Justice Center’s (MRJC) MOUD program), Harborview Medical Center’s Opioid Treatment Network (HMC-OTN) (co-located across five clinic service points), Pathways Clinic, and Sound Health. With the exemption of the MRJC, which is in Kent, WA, all SAIA-implementing sites are based within walking or easy bus-ride distance of one another in central Seattle, where the majority of opioid overdoses occur in King County [1].

JHS has been a provider of MOUD since 2008, when methadone continuation was authorized. Ten years later, in June 2018, buprenorphine continuation was offered to inmates with existing prescriptions. In 2020, a pilot of buprenorphine initiation was conducted in JHS, and in 2021 it was integrated as part of a broader coordinated enhanced discharge program, making JHS an early-adopter of jail-based MOUD provision in the state [37]. JHS is one of the largest jails in Washington, housing ~ 1200 incarcerated people (approximately 10% of Washington’s jailed population) daily [38]. JHS provides MOUD services to ~ 150 patients on any given day; [37] however, gaps in the hand-off between jail and MOUD clinical services upon patients’ release contribute to unacceptable levels of opioid overdoses at this high risk “in-between” time.

HMC-OTN (a UW-affiliate), Pathways (a PHSKC-affiliate) and Sound Health (a community-based mental health non-profit organization) are similarly patient-centered, low barrier clinics, designed to be most accessible for marginalized populations, such as those exiting jail. All community-based clinics offer wrap-around services, including referrals to services that meet patient-identified, non-clinical needs, including housing, food and job-seeking supports. According to clinic managers each clinic sees ~ 150–350 MOUD patients monthly, including approximately 5–10% who are exiting JHS, and most staff have been employed for at least two years.

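### The stated detectable changes of 3.3 and 3.9 points do not follow from 22% and 2,400 per period (the named function gives 3.4 and 4.0), and the counting unit shifts between people, releases and patients

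*Protocol article*

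**What the plan says.** The section on power and sample size in the protocol article says "Our primary analysis will be a difference in proportions test". It assumes a baseline linkage of 22% and "a conservative estimate of 100 people beginning or continuing MOUD in jail and releasing to the community each month", which it equates with "2,400 total releases in each of the baseline and intervention periods". From these it concludes that "we have 80% power to detect a change in the proportion linked of 3.3% percentage points or greater". The corresponding figure it gives for 90% power is 3.9 points. The software is R's power.prop.test. Neither alpha nor sidedness is given, and no allowance for repeated observations is mentioned.

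The Outcomes section asks whether linkage increases from a 24-month baseline to the 24 months after introduction. Table 2 defines the denominator of the primary outcome as the number "of patients on MOUD in jail and released to the community". The Data analysis section speaks of the share of clients linked.

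**The concern.** The paragraph gives almost everything needed to repeat the calculation: baseline, n per period, test and software function. When it is repeated, the answers differ from those printed, and both differences favour the design. This is the only power statement for the primary outcome, and readers will use it to judge what a null result means.

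The second issue is what the 2,400 are. The text moves from people to releases within one sentence, while the outcome is defined per patient. These agree only if nobody is released more than once within a 24-month period. The article gives some reason to doubt that: it speaks of cycles of incarceration, names reduced recidivism as an ultimate aim, and costs recidivism in Table 5. If repeat releases are counted, a test that assumes independent observations misstates the precision. If they are not, the number of analysable patients may be below 2,400.

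**Working it through.** **Inputs.** From the power section: p1 = 0.22; n = 100 per month × 24 months = 2,400 per period; target power 80% and 90%. From the Outcomes section: the hypothesised direction is an increase. Assumed, because not stated: alpha 0.05, two-sided (the function's defaults).

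**Formula.** With d = p2 − p1, p̄ = (p1 + p2)/2, A = √[2p̄(1 − p̄)] and B = √[p1(1 − p1) + p2(1 − p2)]:

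- power = Φ{(√n·d − 1.960·A)/B}
- n per period = [(1.960·A + z_power·B)/d]²

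**Step 1: the stated changes.**

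- d = 0.033 (p2 = 0.253): A = 0.6009, B = 0.6005, √2400 × 0.033 = 1.6167. Power = Φ{(1.6167 − 1.1778)/0.6005} = Φ(0.731) = 76.8%, against the stated 80%. The n needed for 80% is 2,602 per period, 8.4% above 2,400.
- d = 0.039 (p2 = 0.259): A = 0.6036, B = 0.6029, √2400 × 0.039 = 1.9106. Power = Φ{(1.9106 − 1.1829)/0.6029} = Φ(1.207) = 88.6%, against the stated 90%. The n needed for 90% is 2,515 per period, 4.8% above 2,400.

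**Step 2: solve for the detectable increase at n = 2,400.**

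- 80% power: p2 = 0.2544, an increase of 3.44 points.
- 90% power: p2 = 0.2599, an increase of 3.99 points.

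Running power.prop.test in R itself gives the same values. They round to 3.4 and 4.0, so rounding does not explain 3.3 and 3.9.

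**Step 3: can another reading recover the printed pair?**

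| Variant | 80% power | 90% power |
|---|---|---|
| Stated inputs, increase, two-sided 0.05 | 3.44 | 3.99 |
| Decrease instead of increase | 3.26 | 3.75 |
| One-sided 0.05 | 3.04 | 3.60 |
| Continuity correction | 3.48 | 4.04 |
| Unpooled variance, or arcsine | 3.44 | 3.99 |
| Variance held at the 22% rate in both periods | 3.35 | 3.88 |
| 20% baseline, n = 2,400 | 3.33 | 3.87 |
| 22% baseline, n = 2,550 | 3.33 | 3.87 |

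Only the last two rows round to both 3.3 and 3.9, and each changes a stated input. The fixed-variance row comes close (power 78.8% at 3.3 points and 90.3% at 3.9), but it is not what power.prop.test computes. A decrease matches at 80% power only, and the hypothesis is an increase.

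**Step 4: the unit.** The power section multiplies monthly people by 24 and calls the product releases; Table 2 and the Data analysis section count patients or clients. Adding 24 monthly counts gives 2,400 distinct patients only if nobody recurs in that period. The article gives neither releases per person nor a within-person correlation, so no corrected figure can be derived. As an illustration only, take a design effect of 1 + (m − 1)ρ for m releases per person within a period and correlation ρ, both assumed:

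- m = 1.5, ρ = 0.1: design effect 1.05; detectable increase at 80% power 3.53 points.
- m = 2, ρ = 0.2: design effect 1.20; 3.78 points.
- m = 2, ρ = 0.5: design effect 1.50; 4.24 points.

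This formula covers repeats within a period only. A person who appears in both periods contributes positively correlated observations to the two sides of the comparison, which lowers the variance of the difference and works the other way.

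**The case against.** The strongest reply is that the error is trivial. It is about 0.1 point at each power level, and the 90% figure is only 1.4 points of power short. The sample is every eligible person in routine data, not a recruitment target, and the article calls 100 a month conservative. About 106 a month (2,550/24) would give the printed pair. All of this stands as to size, and no design decision turns on it. It does not make the printed figures follow from the printed inputs.

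On the unit, the reply is that the article never says several releases per person are counted. The word releases appears only as a parenthetical gloss, and the choice of index release or of standard errors may be settled in a fuller document. That also stands. A reader might infer that the primary test treats correlated repeat releases as independent and so reports error bars that are too narrow. The article does not support that as fact: such dependence is plausible but not shown, its size is unknown, and correlation across periods would make an independence-based test conservative. What remains is a mismatch of units in the text.

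A reader might also set the 22 linkages a month implied by the power section (100 × 22%) against the Study setting section, where "each clinic sees ~ 150–350 MOUD patients monthly, including approximately 5–10% who are exiting JHS". Three clinics would then see between 3 × 150 × 5% = 22.5 and 3 × 350 × 10% = 105 such patients a month. This is not a contradiction. A monthly caseload can include continuing patients, whereas the power section concerns new linkages within 30 days of release. The lower bound also agrees with 22.

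**Conclusion.** The power statement is wrong as written, by a small amount. From a 22% baseline with 2,400 per period, the detectable increase is 3.4 points at 80% power and 4.0 points at 90%, not 3.3 and 3.9. Power at the printed changes is 76.8% and 88.6%. This rests on two-sided alpha 0.05, on independent observations and on the function the article names. Either the results or an input is in error. A 20% baseline and about 2,550 per period both fit the printed pair, so which one is wrong cannot be settled from the article.

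Separately, people, releases and patients are used interchangeably where they need not be the same, and this needs reconciling. No numerical consequence can be attached to it, and only repeats within a period would widen the error bars. Feasibility is not in question on either count.

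**What to change.** 1. Restate the detectable increases as 3.4 points (80% power) and 4.0 points (90% power). If the baseline or the n per period was misprinted, correct that input instead and rerun the function.
2. State alpha and sidedness.
3. Name one unit and use it in both the power section and Table 2. Either take one release per person per period, with n as the expected number of unique people, or take all releases, with standard errors clustered on the person and an allowance for within-period repeats in the power calculation.
4. Once linked data for the 2022–2023 baseline are available, take the number of releases, the number of people and the share linked from them rather than from assumption.

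The cost is one paragraph and one rerun. The stated detectable change becomes about 0.1 point less favourable if the inputs are kept, and somewhat more if unique people turn out to be fewer than 2,400 per period.
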